## Abstract

**Background:**

New Zealand urgently requires scalable, effective, behavior change programs to support healthy lifestyles that are tailored to the needs and lived contexts of Māori and Pasifika communities.

**Objective:**

The primary objective of this study is to determine the effects of a co-designed, culturally tailored, lifestyle support mHealth tool (the OL@-OR@ mobile phone app and website) on key risk factors and behaviors associated with an increased risk of noncommunicable disease (diet, physical activity, smoking, and alcohol consumption) compared with a control condition.

**Methods:**

A 12-week, community-based, two-arm, cluster-randomized controlled trial will be conducted across New Zealand from January to December 2018. Participants (target N=1280; 64 clusters: 32 Māori, 32 Pasifika; 32 clusters per arm; 20 participants per cluster) will be individuals aged ≥18 years who identify with either Māori or Pasifika ethnicity, live in New Zealand, are interested in improving their health and wellbeing or making lifestyle changes, and have regular access to a mobile phone, tablet, laptop, or computer and to the internet. Clusters will be identified by community coordinators and randomly assigned (1:1 ratio) to either the full OL@-OR@ tool or a control version of the app (data collection only plus a weekly notification), stratified by geographic location (Auckland or Waikato) for Pasifika clusters and by region (rural, urban, or provincial) for Māori clusters. All participants will provide self-reported data at baseline and at 4- and 12-weeks postrandomization. The primary outcome is adherence to healthy lifestyle behaviors measured using a self-reported composite health behavior score at 12 weeks that assesses smoking behavior, fruit and vegetable intake, alcohol intake, and physical activity. Secondary outcomes include self-reported body weight, holistic health and wellbeing status, medication use, and recorded engagement with the OL@-OR@ tool.

**Results:**

Trial recruitment opened in January 2018 and will close in July 2018. Trial findings are expected to be available early in 2019.

**Conclusions:**

Currently, there are no scalable, evidence-based tools to support Māori or Pasifika individuals who want to improve their eating habits, lose weight, or be more active. This wait-list controlled, cluster-randomized trial will assess the effectiveness of a co-designed, culturally tailored mHealth tool in supporting healthy lifestyles.

**Trial Registration:**

Australia New Zealand Clinical Trials Register ACTRN12617001484336; http://www.ANZCTR.org.au/ACTRN12617001484336.aspx (Archived by WebCite at http://www.webcitation.org/71DX9BsJb)

**Registered Report Identifier:**

RR1-10.2196/10789

## Introduction

New Zealand is ranked third in the developed world with respect to obesity rates, with almost one in three New Zealand adults being obese (31.2%) [1]. High body mass index is now the second-ranked avoidable risk to health (after unhealthy diet) for the New Zealand population, accounting for 9.2% of total disability-adjusted life years [2]. Substantial ethnic inequalities exist, with Māori (indigenous New Zealanders; 15% of total population) and Pasifika (collective group of people representing different Pacific Island nations, predominantly from the South Pacific region; 7% of total population) adults living in New Zealand experiencing obesity rates 1.7 and 2.4 times higher than those of non-Māori and non-Pasifika adults, respectively [3].

The determinants of obesity are complex, and Māori and Pasifika are disproportionately affected by socioeconomic and dietary factors that predispose obesity and obesity-related illness [4]. Interventions designed for the general population tend to be less effective for Māori and Pasifika communities [5,6] and may contribute to increased health inequalities [7]. Culturally-tailored interventions are generally more effective [8] and have shown beneficial effects in other countries [9-12]. Nevertheless, funding pressures make it difficult to sustain resource-intensive interventions and maintain long-term health promotion activities.

The broad population penetration of mobile and wireless technologies and advancements in their app offers a potential solution. In total, 92% of New Zealanders own a mobile phone (67% own a mobile phone) [13] and 80% have internet access [14]. Further, there are no significant differences in mobile phone ownership or internet access by ethnicity or education and few differences by age (for those aged <65 years) [13]. Formative research in New Zealand indicates that the majority of Māori would be keen to use an mHealth intervention for weight loss [15], and systematic reviews indicate that mHealth interventions can lead to behavior change [16-19].

mHealth programs (ie, the usage of mobile and wireless technologies designed to achieve medical objectives) [20] have been shown to effectively help people change various health behaviors [19,21-26] and improve other secondary risk factors for cardiovascular diseases, such as blood pressure and medication adherence [27]. Nevertheless, most mHealth programs are designed with minimal input from end-users and lack tailoring to cultural needs. As a result, such interventions often have poor uptake and low rates of use by these communities and end-users [28].

The OL@-OR@ (pronounced “ola ora”) project (ACTRN12617001484336) consists of two stages: a co-design phase and a trial phase. The co-design phase focused on the development of a culturally-tailored, lifestyle support mHealth tool (mobile phone app and website) for Māori and Pasifika communities in New Zealand (conducted between June 2016 and October 2017). Subsequently, a systematic and theory-driven approach was applied to the selection of relevant culturally-tailored behavioral determinants and change techniques, informed by the co-design data gathered. The cluster-randomized trial described in this protocol was co-designed with communities to measure the impact of the OL@-OR@ mHealth tool on key preventable risk factors for noncommunicable disease, specifically diet, physical activity, smoking, and alcohol use.

## Methods

### Co-Design

The trial was designed using the same participatory co-design principles that underpinned the first phase of the OL@-OR@ study. An academic-community partnership has been established guided by the principles of participation and protection and aligned with New Zealand’s Treaty of Waitangi (founding document). Māori- (ie, *kaupapa*) and Pasifika-specific research approaches have been applied throughout the design of the mHealth tool and the trial [29]. Toi Tangata, a Māori health promotion provider, led the engagement process with Māori (involving communities in the Wellington and Auckland regions), and two Pasifika health providers, The Fono in Auckland and South Waikato Pacific Islands Community Services Trust in Tokoroa, led the engagement processes with their local communities. This paper focuses on the OL@-OR@ trial phase. During several *hui* (meetings) attended by Māori and Pasifika community representatives and academics, decisions were made regarding the trial design, including the community-based cluster trial design, the control condition, primary and secondary outcome measures, recruitment methods, and timelines.

### Study Design

This trial protocol adheres to the SPIRIT guidelines (Multimedia Appendix 1). A two-arm, parallel, cluster-randomized controlled trial will be conducted in New Zealand between January and December 2018. The aim is to recruit 1280 participants from 64 clusters (32 Māori, 32 Pasifika); 32 clusters per arm (16 Māori, 16 Pasifika); 20 participants per cluster.

### Eligibility Criteria

The clusters consist of Māori or Pasifika groups or communities identified by the community partners (Multimedia Appendix 2). A cluster was defined as any distinct location or setting in New Zealand where likeminded people or those with shared interests congregate, including a church, *marae* (meeting grounds), school, workplace, sports club, or community group. Individual participants are eligible if they are a member of a participating cluster; reside in New Zealand; are aged ≥18 years; have regular access to a mobile phone, tablet, laptop, or computer; have regular access to internet (at least once a week); are able to provide written consent (e-consent); and have an email address or are prepared to create an email account. Although people within clusters may self-identify as both Māori and Pasifika, for the purposes of the analysis, they will be recorded as Māori if they are part of a Māori cluster and as Pasifika if they are part of a Pasifika cluster.

### Recruitment

Recruitment will be community-led, that is, Māori and Pasifika community coordinators will identify eligible clusters and approach a potential leader within these clusters. Once initial contact has been made with the identified cluster leaders, they will be given information on what is required to be involved with the study, including outlining the process of being randomized to control or intervention conditions. Cluster leaders will then provide informed consent for participation of their group or community in the study. The next step will be for the cluster leaders to begin recruiting individual participants for the trial. Specific recruitment methods will include inviting potential participants to face-to-face information sessions on the trial using social media (eg, Facebook), posters, brochures, other advertising material, and word-of-mouth and inviting established networks and groups previously formed with the community partners.

Potential participants will also be able to enroll in the trial if they are invited by an existing trial participant via the OL@-OR@ tool or if they share a phone with a trial participant who has downloaded the OL@-OR@ tool on that phone.

### Study Procedures

People who are identified as part of a cluster by their local community coordinator will be invited to participate in the study. An information meeting will be organized to provide details about the study and answer any questions that potential participants may have. Potential participants will be provided with a copy of the participant information sheet and brochure. Those who are interested and meet the inclusion criteria may sign up for the study with their local community coordinator. Potential participants who indicate interest will be sent an email with study registration details. By clicking on a link in the email, they will be able to complete their registration details and provide e-consent (participants consenting using a computer-based consent form). They will then complete baseline questions online. Once all questions are complete and the terms of use are accepted, participants will be able to download the OL@-OR@ tool (intervention) or a data collection version of the app (control) on their device. If they do not have a mobile phone or tablet, participants will be able to access a Web version through a link provided. All participants will be asked to use the app (or Web version) for 12 weeks and keep the app running on their device for (at least) the whole 12-week period. At 4- and 12-weeks, Web-based follow-up assessments will take place. After 12 weeks, participants in intervention clusters can continue using the app if they wish. Participants assigned to the wait-list control condition will be able to download the full app or use the Web version once they have completed the 12-week questionnaire.

### Randomization, Allocation Concealment, and Blinding

Clusters will be randomly assigned in a 1:1 ratio to either the intervention or control condition using a computer-generated randomization list prepared by the study statistician. Block randomization will be used with variable block sizes of 2 and 4, stratified by locality (Auckland or Waikato) for Pasifika clusters and by region (rural, urban, or provincial) for Māori clusters to ensure these factors are balanced across the two randomized groups. The randomization list will be concealed until the point of randomization for all clusters. Randomization codes will be kept secure in a restricted computer-based project file and will only be accessible to the project manager and project coordinator who will disclose these to community coordinators when clusters have been identified and participants have signed their agreements. Due to the nature of the intervention, it will not be possible to blind participants or research staff to the use of the different intervention conditions of full versus basic (data collection only) version of the OL@-OR@ tool. The risk of contamination between cluster arms is minimized via selection of distinct clusters located in different settings and communities around New Zealand. The OL@-OR@ system has also been designed so that it is not possible for participants in one arm of the trial (control or intervention) to invite participants in the other arm.

### Study Intervention

#### Intervention Design

The OL@-OR@ tool is designed to help Māori and Pasifika and their *whānau* (extended family) to improve their health and wellbeing by making small positive, culturally relevant changes to their lifestyle. Co-design methods were used to capture and understand the needs of members of Māori and Pasifika communities. These methods fostered expression, reflection, and sharing and informed the development of the intervention.

Ethnic-specific models of health and wellbeing [30-33] were used to interpret the co-design data and to select relevant enablers and barriers of health behavior change, behavior change techniques, and intervention features that align with the cultural needs and wants of its users. The Theoretical Domains Framework [34] and Behavioral Change Taxonomy [35,36] were used to map similarities and differences in identified behavioral determinants and change techniques to those confirming that the OL@-OR@ intervention aligns with evidence-based behavior change principles [37].

Feedback from community focus groups on desired content (physical activity, family, and healthy eating) and themes (holistic wellbeing, connecting, motivation and support, and health literacy) were integrated with established behavioral determinants and change techniques to create the mHealth tool content and features. The design features and proposed functions were presented using wireframes. These were taken back to communities in a continuous two-way iterative improvement process until an agreement was reached that the final wireframe design reflected community wants and needs. A cross-platform (iOS, Android, and Web-based) prototype of the app was created in-house by a team of developers using Apache Cordova and Drupal 8 platforms. The final app was released on Google Play and the App Store.

The tool supports users to set goals and specific steps to reach those goals. Users are encouraged to invite others to join them on their journey and can collect online reward tokens as they achieve their goals. The tool also provides information concerning healthy eating, physical activity, local activities, and health services. Lifestyle trackers help users to monitor their progress (see Multimedia Appendix 3 for screenshot examples of tool features). Regular culturally-tailored reminders and motivational messages (4-5 messages each week) are also sent to motivate users to reach their goals. These messages are delivered via notifications through the app and are stored in the message section of the app. At the beginning of each week, one *whakataukī* (motivational message) will be sent. Lifestyle messages including culturally-tailored tips on eating more healthily, doing more physical activity, reducing stress, improving sleep, and weight loss will be sent weekly. Also, any participants who report that they smoke will receive weekly messages about smoking cessation. Participants will also receive messages highlighting how to use specific features of the tool (weekly) and goal reminders at the end of each week reminding them to review or set new goals (see Multimedia Appendix 4 for examples of motivational messages).

#### Control Condition

Clusters assigned to the control condition will receive a basic version of the OL@-OR@ tool. This version will only collect data (baseline and 4-week and 12-week questionnaires) and provide a weekly motivational message thanking participants for partaking in the study and counting down the weeks until they receive the full OL@-OR@ tool at the end of the 12 weeks. The countdown is to help motivate those in the control group to complete the study. At the end of the study, when all assessments are completed, participants in the control clusters will be able to download the full OL@-OR@ tool to use for as long as they wish. Example screenshots from the control app can be seen in Multimedia Appendix 5.

### Recompense for Involvement in the Study

To acknowledge participants’ time and involvement in the study, *koha* (gift or donation) will be available for each cluster (NZ $500 per cluster of 20 participants, prorated per number of participants recruited for clusters of fewer than 20 participants). The community partners will decide the best way to provide *koha* to the communities involved (eg, provision of a voucher, cash for the community, a donation to a named charity, or purchasing of equipment for the community). Some clusters may elect to share the *koha* equally between enrolled participants.

### Baseline Assessments

At baseline, data will be collected from each cluster concerning the community type (eg, a church community or a sports club), predominant ethnicity in the community, approximate number of community members, approximate number of cluster members interested in participating in the study, and cluster leader and contact details.

In addition, the following data will be collected at baseline from each study participant:

Sociodemographic data: date of birth, gender, ethnicity, hapu (Māori subtribe) and iwi (Māori tribe) where relevant, highest education level, and annual household income.Anthropometric data: self-reported weight (in kilograms) and height (in centimeters).Health status: self-reported health condition(s) defined as being told by a doctor that they have high blood pressure, high cholesterol, diabetes, or heart disease.Physical activity: measured by the Godin Leisure Time Physical Activity Questionnaire [37].Smoking behavior: measured by 7-day point prevalence of self-reported smoking abstinence [38].Alcohol intake: measured by the Alcohol Use Disorders Identification Test Consumption [39].Fruit and vegetable consumption: measured by items used in the New Zealand Health Survey [40].Kava consumption: questions include “Do you consume Kava?,” “How often do you consume Kava?,” and “How many Kava drinks do you consume in a typical week?”Holistic wellbeing (for Māori participants only): Tūhononga (cultural connections), *Mauri* (life force or essence), wellbeing, whanaungatanga (family wellbeing and social connectedness) and Rangatiratanga (self-determination, motivation, and management), measured by 16 questions informed by Māori health models Te Whare Tapa Whā [30] and Te Pae Mahutonga [27] and adapted in part from the Hua Oranga Māori mental health assessment questionnaire [31]. Answers are measured on a 6-point Likert scale.Holistic wellbeing (for Pasifika participants only): spiritual, physical, mental, and family wellbeing measured by 10-items designed for the purpose of this study based on the Fonofale Model [33], the Ottawa Charter and Hua Oranga [32]. All answers are measured on a 5-point Likert scale.Pacific and Kiwi-New Zealand Heritage and Lifestyle (Pasifika participants only): Attitudes and beliefs about Pacific and Kiwi-New Zealand heritage and lifestyle measured using an 8-item cultural affiliation questionnaire [41,42]. Answer categories consist of a 5-point Likert scale.

### Primary Outcome Measure

The primary outcome for the trial is participant adherence at 12-weeks to the recommended health guidelines, as defined by a self-reported composite health behavior score based on the European Prospective Investigation into Cancer-Norfolk Prospective Population Study [38] and as used in a previous trial evaluating the effectiveness of an mHealth-delivered comprehensive cardiac rehabilitation program [43]. This composite score includes: smoking (1: not currently smoking, 0: had ≥1 cigarettes in past 7 days), fruit and vegetable intake (1: ≥5 servings daily, 0: ≤4 servings daily), alcohol intake (1: ≤13 units per week, 0: ≥14 units per week), and physical activity (1: ≥14 units of moderate to vigorous activity/week, 0: ≤13 units of moderate to vigorous activity/week). Scores range from 0 to 4 based on the number of health guidelines met. Participants are classified as adherent if they score 3 or more out of 4 and nonadherent if they score 2 or less. These measures are assessed at an individual level but analyzed and reported at a cluster level (as are the secondary measures).

### Secondary Outcome Measures

Secondary outcome measures will be collected at 4- and 12-week follow-up assessments via a Web-based questionnaire and include the same health behavior outcomes as those assessed at baseline (physical activity, smoking, alcohol intake, and fruit and vegetable consumption) and holistic wellbeing. At 12-week follow-up, user engagement and interaction with the mobile phone app will be quantified using an engagement index [44]. The index is an adapted version of the Web Analytics Demystified Visitor Engagement Index [45]. The original index comprised 7 subindices (click depth, loyalty, recency, interaction, feedback, brand, and duration indices). Although measuring all indices is ideal, the Web Analytics Demystified Visitor Engagement Index protocol emphasizes that the calculation can be adapted to suit the project [45]. Therefore, in line with a previous study assessing user engagement of an mHealth intervention [44], we will select relevant Web metrics to develop a composite engagement index for users of the OL@-OR@ tool. These metrics will include session duration, page views per session, and the number of push notifications. They will be used to calculate the following subindices: (1) click depth index: the number of pages participants view per session in the app, (2) loyalty index: the frequency of participants accessing the app after they commence the intervention, (3) interaction index: the number of push notifications sent through the app that are opened, (4) recency index: time lag between each session when the participant accessed the app, and (5) feedback index: self-reported 20-item measure of participant satisfaction with the app (questions relate to ease of navigation, usefulness of information, helpfulness of notifications, and satisfaction with the look of the app) [44].

The overall engagement index summarizes the subindices from date of registration to 12-week follow-up. The overall index will provide a score for each participant that measures overall engagement with the app during this period. Cutoff points will be developed based on the distribution of the total sample’s index scores using tertiles. Participants will then be categorized as either poorly, moderately, or highly engaged. A summary of all assessments and the stage at which each will be measured is outlined in Table 1.

### Sample Size

Recruiting 640 participants (16 clusters per arm, 32 clusters in total) will provide 80% power at a 5% level of significance (two-sided) to detect a between-group difference of 15% in the primary outcome at 12 weeks postrandomization, assuming the proportion of participants adherent to healthy lifestyle behaviors in the control group is 30% [43] and an intracluster correlation coefficient of 0.05 [46]. The inflation factor is approximately 3, that is, (1+40−1×0.05), which inflates n=160 per arm in a standard randomized controlled trial to n=480 per arm in a cluster-randomized trial under the same assumption. However, we aim to recruit 1280 participants in total from 64 clusters (32 Māori clusters and 32 Pasifika clusters). This sample size will provide 80% power for the analysis of Māori and Pasifika participants separately if our recruitment target is met.

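### The sample size paragraph inflates for clusters of 40 (480 per arm), but the trial plans clusters of 20 and claims 80% power with 320 per arm

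*Protocol article*

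**What the plan says.** The Sample Size section opens with the claim "Recruiting 640 participants (16 clusters per arm, 32 clusters in total) will provide 80% power at a 5% level of significance". The effect to be detected is 15 percentage points over a control proportion of 30%, with "an intracluster correlation coefficient of 0.05". Dividing 640 by 32 clusters gives 20 per cluster, which matches the Study Design section: "32 clusters per arm (16 Māori, 16 Pasifika); 20 participants per cluster". The Abstract gives the same cluster size, and the section on recompense sets the payment for a cluster of 20.

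The next sentence of the Sample Size section puts the inflation factor at about 3, printed as (1+40−1×0.05), "which inflates n=160 per arm in a standard randomized controlled trial to n=480 per arm in a cluster-randomized trial", and says that this is under the same assumption. The paragraph ends with the target of 1280 participants in 64 clusters, half Māori and half Pasifika, which is said to give 80% power for each group analyzed separately.

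**The concern.** One paragraph gives two required sample sizes for one set of assumptions: 320 per arm (640 in total) and 480 per arm (960 in total). The second uses a cluster size of 40, which appears nowhere else in the article and is not presented as an alternative scenario.

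The separate Māori and Pasifika analyses depend on which figure is right. The planned total was doubled to support them, and each has 640 participants, or 320 per arm. If 480 per arm were needed, each would be a third short of its requirement. A reader who takes the inflation sentence at face value would conclude that the 80% claim for each group is unsupported.

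**Working it through.** **Inputs**, from the Sample Size section unless noted:
- two-sided α = 0.05 and power 80%;
- control proportion 0.30 and intervention proportion 0.45;
- intracluster correlation 0.05;
- cluster size m = 20 (Study Design; also 640/32).

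**Step 1: the unclustered sample size.** The unpooled normal approximation is

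n = (z₀.₉₇₅ + z₀.₈₀)² × [p₁(1 − p₁) + p₂(1 − p₂)] / (p₂ − p₁)²

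= 7.849 × (0.21 + 0.2475) / 0.0225 = 159.6, so 160 per arm.

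The protocol's 160 is reproduced. The pooled version gives 163.

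**Step 2: the design effect and what it implies.** The formula is DE = 1 + (m − 1) × ICC.

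| | m = 20 | m = 40 |
|---|---|---|
| DE | 1 + 19 × 0.05 = 1.95 | 1 + 39 × 0.05 = 2.95 |
| 160 × DE, per arm | 312 | 472 |
| 163 × DE, per arm | 317.85 | 480.85 |
| Clusters per arm from 160 × DE | 312/20 = 15.6 | 472/40 = 11.8 |

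With m = 20 the requirement rounds up to 16 clusters of 20, that is 320 per arm and 640 in total. This is the protocol's opening figure. The printed 480 is 160 × 3, with 2.95 rounded up to 3, and it needs m = 40.

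The printed expression also lacks a bracket. Evaluated literally, 1 + 40 − 1 × 0.05 = 40.95. The stated value of about 3 shows that 1 + (40 − 1) × 0.05 was meant.

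**Step 3: power at 320 per arm.** The effective sample size is 320/DE, and power is Φ(0.15/SE − 1.96) with SE = √(0.4575 / effective n).
- m = 20: effective n = 320/1.95 = 164.1. Power is 81.1% (unpooled), 80.4% (pooled), or 78.5% with a t reference on 2 × (16 − 1) = 30 degrees of freedom.
- m = 40: effective n = 320/2.95 = 108.5, in 8 clusters per arm. Power is 63.7% (unpooled), 62.8% (pooled), or 57.5% with a t reference on 14 degrees of freedom.

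**Step 4: power at the printed 480 per arm.** With m = 20 it is about 93%, far above the stated 80%. With m = 40 it is about 80%. The 480 figure therefore matches the stated 80% only for clusters of 40.

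**The case against.** The strongest reply is that the figures governing the trial are correct. The 640 for 80% power is reproduced with clusters of 20, and 1280 is twice that. The randomization and analysis sections do not use the factor of 3 or the 480. On this view it is a slip in an explanatory sentence, a careful reader can resolve it from 640/32 = 20, and the 64% power describes a design that the protocol does not propose. Even a requirement of 480 per arm would be met in the overall comparison, which has 640 per arm. The missing bracket is plainly typographical.

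Most of this stands. The trial is not underpowered on its stated inputs, the 64% is conditional on clusters of 40, and the bracket is not a separate error. Twenty is also a planned size rather than a fixed one: the section on recompense foresees smaller clusters, and the Recruitment section lets participants join by invitation through the tool.

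The contradiction remains. The paragraph offers 40 as the explanation of its own result, labels no alternative scenario, and states a requirement that the separate ethnic-group analyses do not meet. That a reader can work out which figure was meant does not make the printed one correct.

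**Conclusion.** The concern holds. The inflation factor of about 3 and the 480 per arm belong to clusters of 40, while the trial and its 80% power claim belong to clusters of 20. The correct factor is 1.95 and the requirement is 312 per arm (318 with the pooled formula), met by 16 clusters of 20. The printed requirement exceeds the 320 per arm available to each ethnic-group analysis by 160, or 50%.

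This rests on the protocol's own inputs (30% versus 45%, intracluster correlation 0.05, equal clusters of 20) and on the normal approximation. Power at 320 per arm is then 80 to 81%; a t reference gives 78.5%, so the margin is thin. The fault is in the written justification of the primary-outcome sample size and does not affect the recruitment target.

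**What to change.** Replace the inflation sentence with wording such as: The inflation factor is 1 + (20 − 1) × 0.05 = 1.95, which raises the 160 per arm of an individually randomized trial to 312 per arm; this is rounded up to 16 clusters of 20 per arm (320 per arm, 640 in total) for each ethnic group. Remove the factor of 3 and n=480.

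If clusters of 40 were in fact intended somewhere, the authors should say where, and reconcile that with the cluster counts and the power claim.

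The cost is one corrected sentence in the protocol, and in the registry entry if that repeats it (the entry was not available to check). Enrolment, the number of clusters and the analysis stay as they are.
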